## Abstract

**Background:**

Anorexia nervosa (AN) is a severe psychiatric disorder frequently marked by poor treatment response and chronic progression toward rigid, restrictive behaviors. These features highlight the need for innovative strategies targeting core mechanisms and symptoms of the disorder. This feasibility trial evaluates individualized intermittent theta-burst stimulation (iTBS) of the posterior parietal cortex (PPC) as an adjunct to treatment-as-usual, with the goal of identifying patient-specific targets and paving the way for personalized neuromodulation in AN.

**Methods:**

Thirty-four adults with AN (≥18 years, illness ≥12 months, ≥1 prior unsuccessful treatment) will be randomized (1:1) to 20 sessions of real or sham iTBS over 4 weeks. Stimulation will be delivered with a MagPro system and a Cool B70 A/P active/sham coil; motor threshold will be estimated with the Stochastic Approximator (SAMT) and re-checked weekly. Individualized stimulation target will be defined based on resting state functional magnetic resonance imaging data to identify the cortical region within the PPC that is maximally functionally connected with the activity of two meta-analytically derived networks representing body representation and implicit behavioral tendencies. Coil placement will be neuronavigated on individual T1 magnetic resonance imaging (MRI). Assessments will take place at baseline (T0), post-treatment (T1), and 4-month follow-up (T2), covering clinical status (body mass index (BMI), psychopathology, and quality of life), experimental tasks (implicit body representation, peripersonal space, approach–avoidance tendencies toward food, interoceptive accuracy, and neurocognitive functioning), and MRI. Feasibility endpoints include recruitment, retention, completion, blinding, and tolerability. Ethics approval: 6168/EST/25; registration: NCT07106645.

**Discussion:**

This trial emphasizes individualized PPC targeting and rigorous motor threshold (MT) estimation to advance personalized neuromodulation in AN. Feasibility and effect-size data will guide a confirmatory randomized clinical trial, while mechanistic analyses will test whether targeted iTBS strengthens body-schema circuits and aligns neural changes with clinical improvement, supporting a precision-psychiatry approach to eating disorders.

**Trail registration:**

https://clinicaltrials.gov/study/NCT07106645, identifier NCT07106645.

## Introduction

Anorexia nervosa (AN) is a severe and often enduring psychiatric disorder defined by a broad constellation of symptoms, among which two assume a central and defining role: the persistent restriction of caloric intake and profound disturbances in the experience of one's own body (American Psychiatric Association, 2013). Current therapeutic strategies rely on a multidisciplinary framework in which psychological interventions remain the cornerstone, while pharmacological and other biological treatments are mainly directed toward comorbid dimensions rather than the disorder's core pathology (Zipfel et al., 2015). Yet, despite these integrative approaches, a substantial proportion of patients fail to achieve full and sustained remission (Solmi et al., 2024). The combination of a protracted illness trajectory and repeated non-response to standard treatments often delineates forms of AN that become increasingly refractory to clinical intervention. From a cognitive perspective, this refractoriness is reflected in a progressive increase in rigidity and inflexibility while, on the behavioral plane, restrictive eating tends to crystallize into stereotyped, habit-like patterns (Treasure et al., 2020). Disturbances in body experience, in turn, manifest across multiple domains, ranging from dissatisfaction with body image to alterations in bodily perception, distortions of the body schema, and impairments in multisensory integration (Gadsby, 2017; Gentili et al., 2025). The trajectories through which these facets evolve over the course of illness remain incompletely understood. However, it is plausible that the more implicit dimensions of corporeal experience, such as the one related to body schema, remain especially resistant to psychotherapeutic interventions that rely on explicit, verbally mediated processes. These mechanisms contribute to the increasing independence of core symptoms from higher-order cognitive control, thereby reinforcing their chronicity, and treatment resistance.

Contemporary frameworks, including the Research Domain Criteria (RDoC) initiative and precision medicine paradigms, call for a reconceptualization of psychiatric disorders through neurobiological and neurocognitive perspectives, situated within dimensional and mechanistic models of psychopathology (Williams et al., 2024). Within this perspective, symptoms are no longer regarded as descriptive epiphenomena, but as emergent properties of dysfunctional neural circuits and altered cognitive processes (Buckholtz and Meyer-Lindenberg, 2012). The task of clinical neuroscience is therefore to delineate these mechanisms at behavioral, cognitive, and neurobiological levels, and to develop interventions capable of addressing them in a targeted and informed manner. Neuromodulation techniques such as transcranial magnetic stimulation (TMS) and transcranial direct current stimulation (tDCS) hold considerable promise in this respect, given their potential to selectively engage and modulate cortical networks implicated in the genesis and maintenance of symptoms (Liu and Wang, 2024). Their clinical impact rests on how thoroughly the underlying pathophysiological substrates are elucidated, characterized, and selectively targeted.

In AN, the application of neuromodulation remains at an early stage, particularly when contrasted with the more established use of these interventions in conditions such as major depressive disorder or obsessive–compulsive disorder (Rosson et al., 2022). To date, most studies have targeted the dorsolateral prefrontal cortex (DLPFC), based on its role in executive control, affect regulation, and top-down modulation of eating behavior. Preliminary evidence indicates that stimulation of the DLPFC can ameliorate core eating disorder psychopathology and comorbid affective symptoms, supporting its therapeutic relevance (Bahadori et al., 2025; Dalton et al., 2020). Nevertheless, the current evidence base is constrained by small sample sizes and methodological heterogeneity (Collantoni and Favaro, 2024). Moreover, while the DLPFC has been the most commonly targeted region, this choice has not been based on a direct link to the core symptoms of AN. In other clinical populations, selecting stimulation targets according to disorder-specific neurobiological knowledge has proven to be a promising and mechanistically informed strategy (Vinod et al., 2024). Therefore, a critical step for the advancement of neuromodulation in AN is to move beyond prefrontal targets and adopt alternative conceptual frameworks that can better capture the implicit dimensions of the disorder. Traditional interventions, both psychotherapeutic and pharmacological, have intrinsic limitations in this regard. Those psychotherapies that are grounded in explicit and reflective processes are poorly equipped to influence mechanisms that operate outside of conscious awareness, such as those shaping body representation or implicit learning. Conversely, pharmacological agents, while often effective in attenuating comorbid anxiety or depressive symptoms, show limited impact on the core features of AN, namely caloric restriction and disturbances in the experience of one's own body. This asymmetry underscores the need for novel interventions that can directly engage the neural substrates sustaining these implicit and more insidious symptoms.

Emerging theoretical accounts suggest that restrictive eating in AN cannot be fully explained as a purely goal-directed or intentionally maintained behavior, but may also involve automatic, stimulus-driven processes (Steinglass and Walsh, 2016). Such automatic responding is thought to arise from aberrant interactions between fronto-striatal and fronto-parietal systems, with posterior parietal regions contributing to the binding of sensory salience to action and to the automatization of behavioral routines (de Wit et al., 2012). This perspective positions restrictive eating not simply as a voluntary choice but as an entrenched behavioral pattern, resistant to change once consolidated.

With respect to body representation, it is well established that it is a multifaceted construct supported by a distributed network of cortical regions, including unisensory areas involved in body-related perception, motor and premotor regions supporting action-related and motor simulation processes, occipito-temporal regions involved in the visual and semantic representation of the body, and cortical regions implicated in self-referential processing within the default mode network, such as the posterior cingulate cortex (Azañón et al., 2016; Davey et al., 2016; Downing et al., 2001) rather than reflecting an impairment in a single body-related function, a substantial body of research has emphasized that disturbances in body experience in AN extend across multiple domains, including dissatisfaction with own body image, distortions in body size perception, and alterations in body schema and implicit body representations (Gadsby, 2017; Meregalli et al., 2022). Within this framework, regions that support the integration of different bodily information become particularly relevant. The posterior parietal cortex (PPC) represents a key associative hub within this distributed network, as it has extensive connections with motor and premotor cortices and integrates information coming from different sensory modalities to construct and update multisensory body representations, influencing body schema, body ownership, and the representation of the body in space (Chancel et al., 2022; Morasso et al., 2015). Consistently, several studies have suggested that, in patients with AN, alterations in PPC activity may be associated with distortions in body size estimation and broader disturbances in body representation (Mohr et al., 2010; Nico et al., 2010). Taken together, these perspectives converge on the PPC as a promising and underexplored target that bridges two symptom dimensions fundamental to AN: the rigidity of restrictive behaviors and the disturbances of body representation. The present protocol describes a randomized controlled trial (RCT) investigating the effects of real vs. sham stimulation over the PPC in patients with AN, delivered as an adjunct to treatment as usual (TAU). For each participant, the exact stimulation target will be individualized based on resting-state functional connectivity, with the aim of identifying the posterior parietal node showing the strongest connectivity with networks known to be involved in body representation and implicit behavioral tendencies. Participants will be randomly assigned to receive 20 sessions of either sham or real intermittent theta-burst stimulation (iTBS), a patterned TMS protocol thought to enhance cortical excitability in the target region and facilitate long-term neural plasticity (Huang et al., 2005). Importantly, the choice of the standard iTBS temporal pattern is primarily driven by its well-established plasticity-inducing properties, rather than by an assumption of a target-specific pathological theta rhythm in PPC. By directly engaging neural systems underlying the automatization of restrictive eating and the distorted body representation, this study aims to provide a mechanistically grounded therapeutic approach for patients with AN, while advancing the broader development of precision neuromodulation strategies in eating disorders. Outcome measures will be assessed at baseline, immediately after treatment, and at a 4-month follow-up. These will include: (1) a clinical evaluation conducted by an independent psychiatrist not involved in the study; (2) standardized clinical scales; (3) a neuroimaging protocol comprising both structural and functional measures; and (4) a battery of behavioral tasks.

The primary outcome of the study will be clinical improvement, assessed quantitatively through changes in BMI and scores on eating disorder psychopathology questionnaires, and qualitatively through the clinical judgment of the psychiatrist. We hypothesize that patients assigned to the active stimulation group will show greater BMI increase and greater reduction in psychopathology compared to the sham group.

Given that the stimulation protocol was specifically designed to target body representation and automatic tendencies toward food, secondary outcomes will focus on these aspects. Changes in body representation will be assessed using both an implicit task, which provides a measure of patients' perceived body boundaries, and an explicit task, in which patients will be asked to select the silhouette that best represents their own body. We hypothesize that, following the stimulation protocol, patients will show a more accurate representation of their body, selecting a silhouette closer to their actual body and demonstrating more precise boundary estimations.

Implicit behavioral tendencies toward food will be assessed using an approach–avoidance task. In a previous study, we observed that patients with AN exhibited a reduced tendency to approach food stimuli (Meregalli et al., 2024). We expect that, following the stimulation protocol, a more natural behavioral tendency will be restored, characterized by faster automatic approach of food stimuli.

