#### Clinical evaluation

At all three time points, an independent psychiatrist will conduct a semi-structured interview, systematically addressing expectations and concerns about TMS, anxious and depressive symptoms, daily functioning and quality of life, ruminative and repetitive thoughts, and core eating disorders psychopathology. Additional domains such as obsessive-compulsive symptoms, impulsivity levels, and levels of insight will be explored if clinically relevant. This qualitative assessment will complement standardized scales in evaluating symptom change and treatment acceptability. From this interview, the following outcome measures will be extracted: body weight and BMI, presence or return of menses, and any modification of the psychopharmacological treatment. In addition, the psychiatrist will record changes in eating behaviors (restriction, binge episodes, purging, and excessive compensatory exercise), levels of preoccupation with weight and body image, mood and anxiety severity, and global clinical impression (CGI-S/CGI-I). These measures will provide complementary indicators of treatment response and acceptability alongside standardized scales.

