#### Clinical, behavioral and cognitive outcomes

Analyses will be conducted according to the intention-to-treat principle. For each outcome, longitudinal changes will be evaluated using linear mixed-effects models (LMMs) with fixed factors of Group (active vs. sham), Time (baseline, post-treatment, 4-month follow-up), and their interaction (Group × Time). Random intercepts for participants will be included to account for within-subject correlations across repeated measurements. Effect sizes and 95% confidence intervals will be reported alongside p-values.

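### A trial labelled feasibility has a multi-measure efficacy primary outcome with no single variable or success rule, so the stated α = 0.05 and 80% power are not both assured

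*Protocol article*

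**What the plan says.** The abstract's Background opens with "This feasibility trial evaluates individualized intermittent theta-burst stimulation (iTBS) of the posterior parietal cortex (PPC) as an adjunct to treatment-as-usual". Its Methods paragraph adds "Feasibility endpoints include recruitment, retention, completion, blinding, and tolerability", and its Discussion paragraph says "Feasibility and effect-size data will guide a confirmatory randomized clinical trial".

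The closing part of the Introduction gives a different main purpose: "The primary outcome of the study will be clinical improvement, assessed quantitatively through changes in BMI and scores on eating disorder psychopathology questionnaires". To this it adds a qualitative part, which rests on what the psychiatrist judges clinically. It follows this with a directional hypothesis of more BMI gain and a larger fall in psychopathology under active stimulation. The questionnaires are in the plural and not named there.

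Participants and recruitment sizes the trial for a single group (2) × time (3) interaction: Cohen's f = 0.25, power 0.80, α = 0.05, correlation among repeated measures 0.5. This gives 28 participants, raised by 20% to 34. The outcome behind f = 0.25 is not named.

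In the Analyses section, Feasibility lists indicators without ranking them as primary. Clinical, behavioral and cognitive outcomes states "For each outcome, longitudinal changes will be evaluated using linear mixed-effects models", with p-values, effect sizes and confidence intervals. The article gives no rule for combining results across measures.

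**The concern.** Two things do not fit together.

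- **Purpose.** The abstract describes a trial whose feasibility and effect-size data feed a later confirmatory trial. The Introduction and the sample size section describe a hypothesis test of efficacy. Good feasibility with null efficacy, or the reverse, has no defined reading.
- **Primary outcome.** It is a construct, clinical improvement, measured by at least BMI, an open number of questionnaire scores and a psychiatrist's judgment. The calculation supports one test, while the analysis produces a separate p-value per measure. A result positive on one measure and null on another could be read as success or failure, and the article does not say which.

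At stake is whether the quoted 5% error and 80% power describe the claim the trial will actually make.

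**Working it through.** **Inputs from the protocol article.** Two groups, three time points, f = 0.25, correlation ρ = 0.5, α = 0.05, target power 0.80, N = 28 raised to 34. The number of primary measures and the correlation between them are not given. Both are assumptions here: two or three measures, correlation from 0 to 0.7.

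**1. Reproduce the plan's figure.** For the within–between interaction in a repeated-measures ANOVA, the noncentrality is λ = f²·N·m/(1 − ρ), with m = 3 time points and k = 2 groups. The degrees of freedom are (k − 1)(m − 1) = 2 and (N − k)(m − 1).

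At N = 28: λ = 0.0625 × 28 × 3 / 0.5 = 10.5, with 2 and 52 degrees of freedom, and power is 0.812. At N = 26 power is 0.778. The smallest balanced N is therefore 28, as stated. The allowance is 28 × 1.2 = 33.6, rounded up to 34. The calculation is sound for one test on one variable.

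**2. Any one measure can carry the claim.** Under independence the familywise error is 1 − 0.95^k:
- two measures: 1 − 0.95² = 9.8%
- three measures: 1 − 0.95³ = 14.3%

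With equally correlated 2-degree-of-freedom tests (400,000 simulated draws, large-sample chi-square):

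| Measures | Correlation 0 | 0.3 | 0.5 | 0.7 |
|---|---|---|---|---|
| 2 | 9.8% | 9.5% | 9.2% | 8.4% |
| 3 | 14.3% | 13.8% | 12.6% | 11.1% |

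**3. Two measures must both succeed.** Type I error stays at or below 5%. Under independence, and with f = 0.25 for each measure, joint power at N = 28 is 0.812² ≈ 0.66.

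**4. Any one measure, with Bonferroni.** Power per measure at N = 28 is 0.72 for two measures (α = 0.025) and 0.66 for three (α = 0.0167). Reaching 0.80 needs 34 and 36 completers. Allowing for 20% loss as N/(1 − 0.2), that is 43 and 45 enrolled.

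**5. If all 34 stayed to the end.** Both-required power would be 0.79 for two independent measures. Bonferroni power would be 0.82 for two and 0.78 for three. The plan, however, treats 28 as the number to be analysed and the other six as cover for dropout.

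**6. One named variable.** α = 0.05 and power 0.81 at N = 28 hold unchanged.

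**The case against.** The strongest reply is that nothing in the article says any single success is enough. The Introduction's hypothesis joins BMI and psychopathology with a conjunction, and if both are required α is kept. A multiplicity rule may also sit in an analysis plan that is not shown. Both arguments stand, and they limit the point. A reader might infer that the 5% level is lost or multiplied several times over; the documents do not support that. They show only that it is not assured. The conjunctive reading does not rescue the plan as a whole, though, because it moves the shortfall to power (step 3).

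Three further inferences go too far.

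- **Larger error figures.** Counting the four EDE-Q domains, the Body Shape Questionnaire and a global impression rating as primary tests gives error rates of about 20% or more. The article does not name these as primary, and such figures depend on assumed counts and correlations.
- **A primary that cannot be modelled.** Menstrual status and CGI-I do not suit a linear mixed model with a baseline level. Neither is named as primary, however, and CGI-S is listed alongside for the same three-visit interview. This is a secondary modelling detail, often left to an analysis plan.
- **Extra tests at T1 and T2.** The stated test is one interaction over three time points. Separate tests at each visit are not planned.

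It can also be said that a trial meant to inform a later one needs less strict error control. That would be a good answer if the article declared efficacy exploratory. Instead it declares efficacy primary and powers it at 80%.

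**Conclusion.** The point holds in a limited form. The article states two main purposes, and it fixes the primary outcome badly by leaving it as several measures with no named variable or success rule. Defining the primary outcome is a core protocol item, so an unseen analysis plan does not excuse this.

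The stated sample size is correct for one test. With two primary measures and 28 analysed, no reading delivers both α = 0.05 and 80% power: the error is about 8–10%, or joint power is about 0.66, or Bonferroni power is 0.72. With three measures, the any-success error is about 11–14%.

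These sizes assume two or three measures, correlation between 0 and 0.7 for the error rates, independence for the joint power, and the plan's f = 0.25 for every measure. They use the repeated-measures ANOVA calculation and large-sample tests rather than the mixed model itself.

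**What to change.** Reconcile the abstract with the Introduction, then choose one of two routes.

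- **Efficacy primary.** Name one variable, for example BMI, and test it by the group × time interaction that the sample size section already powers. N = 28/34 and α = 0.05 then stand. Test the EDE-Q global score next, at the same level, only if the first test succeeds. Report the other scales and the psychiatrist's judgment as secondary or descriptive. The 80% power applies to the first test only. State that f = 0.25 refers to the named variable.
- **Feasibility primary.** Say so in the Introduction and report efficacy as effect estimates with 95% confidence intervals, without a claim of success. This fits the abstract's stated use of the data.

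If a contrast at T1 alone is preferred to the interaction, restate the power for it, because the present calculation does not cover it. If two or more measures are to stay primary, state whether any or all must succeed and redo the sample size accordingly.

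The cost of either main route is a change of wording in the protocol and any matching registration entry, with no change to the sample size. The downside is that fewer measures can be called primary.

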## Methods

### Design

This study will adopt a double-blind, parallel-group, randomized controlled design with two arms. Patients with AN will be randomly assigned to undergo 20 consecutive weekday sessions of either real iTBS (treatment arm) or sham iTBS (control arm). Outcome assessments will take place at three time points: baseline (T0), immediately after the intervention (T1), and at a 4-month follow-up (T2). After completing the follow-up, participants allocated to the sham control arm will be given the option to receive real iTBS.

